#### Assessment Appointments

Four assessment appointments are scheduled: at baseline, 6 weeks, 6 months, and 12 months. Assessment appointments can occur on the same day as treatment appointments.

##### Baseline Assessment

During the baseline assessment, the vulva will be examined for LS, and vulvoscopy will be performed to assess for signs of vulvar malignancy. A 3-4 mm vulvar biopsy under a local anesthetic will be performed to confirm the diagnosis of LS for participants without prior biopsy-proven evidence. The investigator scores the patients’ LS by using the clinical scoring system, and the participant completes the Visual Analogue Scale, the Australian Pelvic Floor Questionnaire, and the Dermatology Life Quality Index. Deidentified clinical photos are taken.

##### Assessments at 6 Weeks, 6 Months, and 12 Months

At each assessment appointment, the investigator performs a vulvoscopy and scores the participant’s LS by using the clinical scoring system. The participant completes the Visual Analogue Scale, the Australian Pelvic Floor questionnaire, and the Dermatology Life Quality Index questionnaire. Deidentified clinical photos are taken at each appointment. Additionally, participants are asked if they experienced symptoms requiring the use of topical steroids. The completed documents are placed in the patient’s folder and remain onsite in a locked cabinet inaccessible to clinical investigators. Documentation will be accessible by a nonclinical research assistant who will be responsible for entering the collected data into the trial’s SPSS database for statistical analysis. At the final assessment consultation, participants are discharged to the care of their referring physician. At the conclusion of data analysis, the participant and the investigators will be informed about the treatment allocations during the study. Participants will receive a letter about the research findings.

### Outcome Measures

#### Primary Outcome Measure

The primary outcome of this study was to compare the efficacy of PRP and saline injections by evaluating the change in the LS clinical score across groups at 3 timepoints: 6 weeks, 6 months, and 12 months (Table 1). The clinical scoring system for LS is an objective, validated, physician-administered assessment measuring the severity of vulvar LS [18]. Six clinical characteristics are graded on a 3-point Likert scale with grade 0 as normal, grade 1 as moderate changes, and grade 2 as severe changes. The clinical characteristics are erosion, hyperkeratosis, fissures, agglutination, stenosis, and atrophy. Scores range from a minimum of 0 to a maximum of 12; a score ≥4 identifies LS with a probability of >90% in conjunction with the participant experiencing intractable symptoms such as pruritus, dyspareunia, soreness, or burning [22].

**Table 1 table1:** Clinical scoring system for vulvar lichen sclerosus.

Clinical characteristic	Grade 1 (moderate)	Grade 2 (severe)
Erosion	1-2 small erosions, almost not macroscopically visible	Macroscopically visible and/or >2 or confluent lesions
Hyperkeratosis	≤10% vulva and perineum affected	>10% vulva and perineum affected
Fissure	Rhagades affecting the posterior introitus	Generalized vulvar rhagades
Agglutination	Partially affecting preputium clitoridis and labial minora	Complete agglutination of both labia minora or majora
Stenosis	Narrowing of introitus, which could still be passed by 2 fingers	Narrowing, which could be passed by less than 2 fingers
Atrophy	Shrinking of labia and clitoris	Labia minor and clitoris were no longer visible

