**Methods:**

This is a protocol for a 12-month, single-center, parallel-group, double-blind, randomized controlled trial evaluating the efficacy of PRP for LS compared to saline. Adult female patients with biopsy-proven LS who are otherwise in good health but are nonresponders to topical steroid treatment prior to inclusion are eligible for the trial. A total of 68 participants will be randomly allocated via a random number generator to receive either PRP or saline injections to areas of the vulva with LS. All participants will be blinded to the intervention received. Participants will be followed up with assessments of clinical LS signs, subjective symptom scores, and quality of life questionnaires by blinded assessors at 4 timepoints: baseline, 6 weeks, 6 months, and 12 months. The primary outcome is the clinical scoring system for LS—the total LS score.

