#### Treatment Appointments

Two treatment appointments are scheduled: at baseline and 6 weeks later. After administering the treatment, the following data are recorded on the treatment record form: date, participant name and date of birth, unique study identifier, verification of venous blood collection, 2-person verification of treatment syringe contents, 2-person verification of injection of treatment syringe, and adverse reactions.

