#### Sample Size and Power Calculations

Sample size calculations are based on the pilot study on 28 patients [20], in which 80% of the participants treated with PRP experienced an improvement in their symptoms. Assuming a difference of 30% between PRP and normal saline at 12 months, an α risk of 5%, and a power of 80%, a sample size of 31 participants for each group is required. Assuming that 10% of the participants withdraw or are lost to follow-up, a sample size of 34 participants for each group is required or a sample size of 68. The pilot study used subjective symptom improvement as its primary outcome, whereas this trial’s primary outcome is the LS clinical score, an objective physician-rated measure. Although these outcomes differ, symptom improvement in the pilot study was used as a surrogate to estimate a conservative effect size for this study, given the lack of prior data on LS clinical score changes with PRP. This study will also evaluate secondary outcomes, including subjective symptom scores, allowing for comparisons between subjective and objective measures.

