### Statistical Analysis

All analyses will be conducted using SPSS software (IBM Corp). We will perform analyses using the intention-to-treat principle. Outcomes will be compared within groups over time and between groups at baseline, 6 weeks, 6 months, and 12 months. Baseline characteristics will be summarized using descriptive statistics, and a comparison of the 2 treatment arms will be assessed by 1-way analysis of variance or 1-sided *t* test for continuous variables or nonparametric alternatives if data are not normally distributed. The Shapiro-Wilk test will be used to assess if data are normally distributed. For all tests, a significant level of α=5% is applied. The analysis of changes compared to the baseline will test the null hypothesis that there is no difference between the 2 timepoints. Further analyses between the groups will test the null hypothesis that there are no differences between the 2 groups at one timepoint. Missing value analysis will be performed, and missing values will be imputed using expectation maximization. Analyses will be conducted in line with the intention-to-treat principle, which will be compared to per-protocol analyses.

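### Three visits share primary status and each is tested at 5% with no order or adjustment, while the sample size rests on one 5% test at 12 months

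*Protocol article*

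**What the plan says.** The article makes four statements that bear on this point.

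- **Primary Outcome Measure:** the outcome is assessed by "evaluating the change in the LS clinical score across groups at 3 timepoints: 6 weeks, 6 months, and 12 months". All three visits have equal standing. The abstract names the score but no visit: "The primary outcome is the clinical scoring system for LS—the total LS score".
- **Statistical Analysis:** "Outcomes will be compared within groups over time and between groups at baseline, 6 weeks, 6 months, and 12 months". The between-group hypothesis concerns a single visit: "Further analyses between the groups will test the null hypothesis that there are no differences between the 2 groups at one timepoint". The level is common to all: "For all tests, a significant level of α=5% is applied". The section describes no joint test over time, no testing order and no adjusted level.
- **Sample Size and Power Calculations:** "Assuming a difference of 30% between PRP and normal saline at 12 months", with one 5% alpha and 80% power. This is the only place where one visit is singled out.
- **Treatment Appointments:** "Two treatment appointments are scheduled: at baseline and 6 weeks later". The Assessment Appointments section places an assessment at 6 weeks too and allows it on the day of treatment.

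**The concern.** Read together, the outcome definition and the analysis section create three primary between-group tests at 5% each, and nothing says how the three results combine into one conclusion. A report could rest its efficacy claim on whichever visit crosses 5% and still follow the article's wording.

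The sample size was derived as if one comparison at 12 months decided the trial. The design and the analysis therefore describe different primary claims.

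The 6-week visit raises a further question of interpretation. Its score is taken at the visit where the second treatment is scheduled, so a difference there speaks to essentially one treatment, not the two-treatment course. That does not add to the error rate. It does mean that a lone 6-week result could be presented as the primary finding for a course that participants had not yet completed.

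**Working it through.** **1. The plan's own figure.** Inputs from the sample-size paragraph: 80% improved on PRP, a difference of 30 points (so 50% on saline), alpha 5%, power 80%. With pooled variance and no continuity correction,

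n = [z_α √(2 p̄(1−p̄)) + z_β √(p₁(1−p₁) + p₂(1−p₂))]² / (p₁−p₂)²

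Here p̄ = 0.65, √(2 × 0.65 × 0.35) = 0.6745 and √(0.16 + 0.25) = 0.6403.

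- One-sided 5%: (1.645 × 0.6745 + 0.842 × 0.6403)² / 0.09 = 30.2, so 31 per group. This is the stated figure.
- Two-sided 5%: (1.960 × 0.6745 + 0.842 × 0.6403)² / 0.09 = 38.5, so 39 per group.

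The stated 31 therefore allows for one test at 5% and no multiplicity. It matches only a one-sided test, so both kinds of sidedness are shown below.

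**2. Three tests at 5%.** Inputs: three visits (Primary Outcome Measure) and 5% per test (Statistical Analysis). If the tests were independent, the chance of at least one false positive would be

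1 − (1 − 0.05)³ = 1 − 0.857 = 14.3%

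**3. Correlated visits.** The same participants are scored at each visit, so the tests are positively correlated. The article gives no correlation. Assuming three jointly normal test statistics with a common correlation:

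| Correlation (assumed) | Two-sided | One-sided |
|---|---|---|
| 0 | 14.3% | 14.3% |
| 0.5 | 12.5% | 11.8% |
| 0.7 | 10.9% | 10.3% |
| 0.9 | 8.4% | 8.0% |

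**4. A reasonable central value.** The outcome is a change from baseline. If all visits have equal variance σ² and equal pairwise correlation ρ, each change score has variance 2σ²(1−ρ), and any two change scores have covariance σ²(1−ρ). Their correlation is 0.5 whatever ρ is, because they share the baseline. That points to about 12.5% two-sided. Simulated t tests on change scores with 17 and with 34 per arm gave about 12.5-13%.

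**5. The alternatives.** One designated visit restores 5% and leaves n unchanged. Keeping all three visits primary with Bonferroni (0.05/3 = 0.0167 each) holds the error at or below 5%. On the protocol's own assumptions, the formula in step 1 then gives 44 per group one-sided (43.3 rounded up) or 52 two-sided (51.5 rounded up). The Results section reports 34 participants recruited in total.

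**The case against.** Several points can be made for the plan.

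- **Any single visit counting as success is not stated.** A reader might infer that the error rate of the primary claim simply is 11-13%. The documents do not support that. They give no success rule and no correlation, and the range 11-13% corresponds to assumed correlations of about 0.4-0.7 with two-sided tests. If all three visits had to be significant, the rate would be below 5% (about 0.3% at correlation 0.5 and about 2% at 0.9). This stands, and the size must be stated conditionally.
- **Sidedness is unclear.** The only sidedness mentioned is in "1-way analysis of variance or 1-sided *t* test for continuous variables", in the sentence on baseline characteristics and comparison of the arms. One-sided rates are slightly lower, but the conclusion is the same.
- **An analysis plan that is not shown may set an order or an adjustment.** It may, and silence alone would be no finding. The article is not silent, however. It makes three visits primary and fixes 5% for every test. A plan that named one visit or lowered the level would contradict this text.
- **The sample-size paragraph already points to 12 months.** It does, but a reader who infers that 12 months is the designated primary analysis goes too far. The paragraph uses a symptom-improvement proportion, which it calls a surrogate, and not the total LS score. The timepoint is not carried into the outcome definition or the analysis.
- **It is late to change.** The study is closed and data are being analysed. Allocation is to be disclosed to participants and investigators only when data analysis is complete, so a prior designation may still be possible, but the article does not establish this.

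**Conclusion.** The point holds in conditional form. The article gives three visits primary status, tests the groups one visit at a time at 5%, and sizes the trial for a single 5% comparison at 12 months. These statements do not describe one primary claim.

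If any one significant visit may support efficacy, the false-positive rate is about 8-14% instead of 5%, with about 12.5% a reasonable central value for two-sided tests on change from baseline. This rests on three assumptions that the article neither states nor excludes: that one visit suffices, a common between-visit correlation from 0 to 0.9, and the sidedness of the tests. Under the first assumption, the rate exceeds 5% throughout that range, one-sided or two-sided.

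**What to change.** Before any between-arm results are seen, designate the between-arm difference in change in total LS score at 12 months as the single primary analysis. This matches the timepoint of the sample-size paragraph, though not its endpoint. Make 6 months and 6 weeks secondary, reported as estimates with confidence intervals, and state that the 6-week score reflects essentially one treatment. Other schemes, such as a fixed testing sequence or an adjusted level, would also control the error, but an adjusted level needs more participants than were recruited.

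Date the decision and disclose that it was made after data collection. If between-arm results have already been seen, label the designation post hoc.

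The cost is a short amendment to the outcome and analysis sections, plus that disclosure. The sample size does not change. The downside is that an effect seen only early can no longer support the primary claim.

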#### Secondary Outcome Measures

Secondary outcome measures will compare changes in the subjective assessment scores over time within each group and between groups. Participants will complete the Australian Pelvic Floor Questionnaire and Dermatology Life Quality Index at each assessment appointment to evaluate changes in the subjective disease burden. The Australian Pelvic Floor Questionnaire is a validated self-administered questionnaire assessing pelvic floor symptoms, including bladder, bowel, prolapse, and sexual function symptoms, as well as symptom severity and impact on quality of life [23]. The Dermatology Life Quality Index is a validated tool assessing quality of life impairment for people experiencing inflammatory skin conditions, and a change in the score of at least 4 points is considered clinically significant [24]. A Visual Analogue Scale will be presented to participants at each assessment to record the severity of their symptoms. Participants will be asked to indicate their level of distress in relation to 2 symptoms: pruritus and dyspareunia.

The additional secondary outcomes are safety and adverse events of receiving the treatment. Autologous PRP has an advantageous safety profile due to the utilization of the patient’s own blood, which minimizes the risk of adverse events or autoimmune reactions [25]. In a pilot study undertaken by the principal investigator, all participants (n=28) reported minimal to mild pain in the 24 hours following the procedure [20]. There were no reported cases of infection, bleeding, hematoma, or other adverse effects. Adverse events will be monitored immediately after receiving the treatment, and at each assessment appointment, participants will be asked if they experienced any adverse events in the preceding period. Any adverse effects will be recorded and reported to the ethics committee.

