### Study Aims

The goal of this study is to assess the safety and efficacy of autologous PRP injections for the treatment of vulvar LS compared to saline injections.

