#### Injection Technique

The participant will be asked to lie in the lithotomy position on the examination table, and a topical anesthetic cream will be applied to the vulva 10-20 minutes prior to injection. The clinical nurse will hand the syringe to the clinical investigator who will inject the study preparation into the vulval mucosa in areas affected by LS by using a 30G needle. The amount injected may be less than 4 mL, if on visual inspection, it becomes evident that the tissue cannot hold the maximum amount.

The decision to administer 2 treatment sessions, spaced 6 weeks apart, was based on protocols from previous PRP studies [20,21] in dermatology and gynecology, where 2-3 sessions are commonly used to optimize tissue response and healing. The 6-week interval allows sufficient time for tissue remodeling and the biological effects of growth factors to occur between treatments. The dosage of 4 mL was selected based on the maximum safe and practical volume deliverable to the vulvar tissue, as well as the prior clinical experience in similar interventions to avoid tissue overdistension or adverse effects. The patient will be monitored for adverse effects for 15 minutes after the study treatment and will be advised not to engage in penetrative vaginal sex for 72 hours after the procedure.

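### As described, adverse reactions after the first 15 minutes are captured only by recall, 6 weeks after injection 1 and about 18-20 weeks after injection 2, so mild early reactions are at risk of under-reporting

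*Protocol article*

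**What the plan says.** All references are to the protocol article.

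- **Status of safety.** Study Aims (in the Introduction) says the goal is to "assess the safety and efficacy of autologous PRP injections" against saline. Secondary Outcome Measures lists safety and adverse events as additional secondary outcomes.
- **Capture on the day.** Injection Technique: "The patient will be monitored for adverse effects for 15 minutes after the study treatment". Secondary Outcome Measures repeats this in general terms: "Adverse events will be monitored immediately after receiving the treatment". Treatment Appointments shows that the finding is written down, since the treatment record form ends with "2-person verification of injection of treatment syringe, and adverse reactions".
- **Capture afterwards.** Secondary Outcome Measures: "at each assessment appointment, participants will be asked if they experienced any adverse events in the preceding period".
- **Timing.** Treatment Appointments: "Two treatment appointments are scheduled: at baseline and 6 weeks later". Assessment Appointments: "Four assessment appointments are scheduled: at baseline, 6 weeks, 6 months, and 12 months".
- **What was expected.** Secondary Outcome Measures says of the 28 pilot participants that all "reported minimal to mild pain in the 24 hours following the procedure". It reports no infection, bleeding, hematoma or other adverse effect in that pilot.

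**The concern.** The one reaction that the pilot leads the reader to expect is common, mild and confined to the first day. The trial observes the participant directly for the first quarter of an hour. From then on, the described method depends on what she remembers at the next scheduled assessment, weeks or months later. Brief, minor pain is the kind of event most exposed to recall loss over such intervals.

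Two things are at stake. The first is the between-arm safety comparison: if a share of reactions is forgotten in both arms, the recorded absolute difference is smaller than the true one, and an apparent absence of difference is easier to find. The trial recruited 34 participants against a planned 68 (Results; Sample Size and Power Calculations), so a null safety comparison would be imprecise even with complete capture. The second is any description of tolerability by injection: the two injections have very different recall intervals. The Limitations section mentions that rare adverse events may be missed, but says nothing about recall.

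**Working it through.** The plan states no figure on this point that could be reproduced. The check is calendar arithmetic on the visit schedule, followed by an illustration whose inputs are assumed.

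**Recall intervals**

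Inputs: injections at week 0 and week 6 (Treatment Appointments); follow-up enquiries at week 6, month 6 and month 12 (Assessment Appointments). Interval = date of next enquiry minus date of injection.

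- Injection 1: week 6 - week 0 = 6 weeks = 42 days. This assumes that the 6-week enquiry is made before the second injection.
- Injection 2, month 6 read as week 26: 26 - 6 = 20 weeks = 140 days.
- Injection 2, month 6 read as week 24: 24 - 6 = 18 weeks = 126 days.
- Ratio of the two intervals: 126/42 = 3.0 to 140/42 = 3.3.

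**Direct observation**

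15 minutes out of 24 × 60 = 1440 minutes is 15/1440 = 1.0% of the first day. This is a share of time, not a share of events: the article does not say when within the 24 hours the pilot pain began.

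**Is anything else described that would fill the gap?**

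- The Overview of the Study Intervention section counts 4 appointments in all.
- Data Collection itemises each participant's folder. It lists questionnaires and a study recording sheet, but no diary.
- The Visual Analogue Scale is limited to pruritus and dyspareunia, so it does not rate pain after the injection.

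**Effect of recall loss**

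Let p1 and p0 be the true proportions with a reaction under PRP and saline, and r the proportion of reactions recalled, equal in both arms, with no false reports.

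- Recorded difference = r·p1 - r·p0 = r(p1 - p0).
- Recorded ratio = r·p1 / r·p0 = p1/p0, unchanged.

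The documents give none of p1, p0 or r. Illustration only, with assumed p1 = 60% and p0 = 30%:

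| Assumed r | PRP recorded | Saline recorded | Difference | Ratio |
|---|---|---|---|---|
| 1.0 | 60% | 30% | 30 points | 2.0 |
| 0.8 | 48% | 24% | 24 points | 2.0 |
| 0.5 | 30% | 15% | 15 points | 2.0 |

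For the two injections, r need not be equal, because one interval is at least three times the other. If the true rates were the same and recall were, say, 0.8 after injection 1 and 0.5 after injection 2 (both assumed), the recorded rate after injection 2 would be 0.5/0.8 = 62.5% of that after injection 1, with no real change in tolerability.

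**The case against.** The strongest objections are these.

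- **The first 24 hours are not left out.** A reader might infer that the schedule misses that window altogether. It does not: the question covers everything since the last visit, which includes the first day after the injection. What is lacking is prospective observation. This objection stands.
- **No loss is proven.** A reader might infer that reactions will certainly be under-reported, or that the 1.0% figure puts nearly all of them outside observation. The documents supply neither a recall rate nor the time of onset of the pilot pain, and full recall is not excluded. This stands, so the point can claim a risk and no size. The topical anesthetic might also mask pain during the 15 minutes, but the article gives only its application time, so nothing here rests on it.
- **No arm is favoured.** Both arms follow one schedule, and participants and data collectors are to be blinded (Randomization and Blinding). A reader might infer a bias in favour of PRP; the documents do not support that. Equal loss still shrinks the absolute difference, so the concern survives in that form. More serious events, such as infection, are also more likely to be remembered or to bring the participant back.
- **The full documents may say more.** The article refers post-procedural care to Multimedia Appendix 2. The participant information (Appendix 1), appointment schedule (Appendix 3) and study recording sheet (Appendix 8) are not shown either. Earlier contact cannot be excluded. However, the article states how and when adverse events are collected, and nothing in it points to an additional contact.
- **It is a design choice, and the trial is closed.** Asking at scheduled visits is common and contradicts nothing in the article, and no comparison of the two injections is announced. Recruitment ended in November 2023, so a diary can no longer help this trial. What remains is how the results are reported and how the protocol is reused. The Discussion offers it to other researchers as a standardized protocol.

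**Conclusion.** The point holds as a limitation of adverse-event capture. As described, every reaction arising after the 15-minute observation depends on recall at 42 days (injection 1) and about 126 to 140 days (injection 2), while the pilot's one described reaction fell within 24 hours in 28 of 28 participants. Mild transient local reactions are therefore at risk of under-reporting by an amount that cannot be computed.

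The conclusion rests on three assumptions: that the appendices not shown contain no earlier contact, that recall of minor pain is less than complete at these intervals, and that any loss is similar in the two blinded arms. On these assumptions, recorded rates and absolute PRP-saline differences are too small, ratios are roughly preserved, and reactions to injections 1 and 2 cannot be compared. The primary outcome is unaffected.

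**What to change.** **For the completed trial.** State in the report that reactions after the 15-minute observation were collected by recall at about 6 weeks and about 20 weeks (18 if 6 months is taken as 24 weeks), unless the appendices document earlier contact, in which case describe that contact. Tabulate reactions by arm and by injection number, keeping those entered on the treatment record form separate from those recalled later. Do not conclude comparable tolerability from the recalled events. Add recall to the limitations. The cost is a few sentences and one table; the price is a more guarded safety statement.

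**If the protocol is reused.** Give every participant in both arms a one-page local-reaction diary card at each treatment visit, covering the first 24-72 hours (for example a 0-10 pain rating, bleeding, swelling and signs of infection), returned by post or at the next visit. Report the results by arm and injection number. This changes data collection only. The cost is a printed card, some data entry and a small burden on participants. Reported rates of mild reactions may be higher than under recall and should be read with that in mind.
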